#### **11.3.1.9 Deaths**

Any participant deaths that occur during the study will be considered SAEs and reported as per Section [11.3.6](#). If a death occurs, the investigator may be asked to provide a copy of any post-mortem findings, including histopathology.

#### **11.3.2 Time Period and Frequency for Collecting Adverse Events and Serious Adverse Events Information**

For the purposes of this study, any detrimental change in the participant's condition after signing the ICF and up to completion of the Safety Follow-up Visit (or until withdrawal from the study, whichever is later) will be considered an AE. AEs will be collected at every study visit (Section [3](#), [Table 1](#)). Any relevant observations made prior to the first dose of study treatment are to be

recorded on the AE eCRF but will not be considered TEAEs and will be reported separately from TEAEs.

At any time after completion of the Safety Follow-up, if an investigator learns of an SAE that can be reasonably related to study treatment, they will promptly notify the sponsor.

### **11.3.3 Method of Detecting Adverse Events and Serious Adverse Events**

Care will be taken not to introduce bias when detecting AEs and SAEs. Open-ended and non-leading verbal questioning of the participant is the preferred method to enquire about AE occurrences.

See Section 11.3.1.7 for a discussion of extra-musculoskeletal manifestations of PsA for additional monitoring at the Week 12 Visit, EOT Visit, and Safety Follow-up Visit.

### **11.3.4 Recording of Adverse Events and Serious Adverse Events**

Any AE is to be recorded starting immediately after the participant provides informed consent through the end of the safety follow-up period (or until withdrawal from the study, whichever is later).

When an AE/SAE occurs, it is the responsibility of the investigator to review all documentation (e.g., hospital progress notes, laboratory reports, and diagnostics reports) related to the event. The investigator will then record all relevant AE/SAE information in the eCRF. It is not acceptable for the investigator to send photocopies of the participant's medical records in lieu of completion of the AE/SAE eCRF page. There may be instances when copies of medical records for certain cases are requested. In this case, all participant identifiers, with the exception of the study participant number, will be redacted on the copies of the medical records before submission. The investigator will attempt to establish a diagnosis of the event based on signs, symptoms, and/or other clinical information. Whenever possible, the diagnosis (not the individual signs/symptoms) will be documented as the AE/SAE.

The following variables will be recorded for each AE: verbatim/AE description and date for AE start and stop, intensity (Section 11.3.4.1), seriousness (Section 11.3.1.4), causality rating (Section 11.3.4.2), whether or not the AE caused the participant to discontinue (Section 9.4), any other action (Section 11.3.4.3). Continuous events should be recorded at the maximum severity observed.

Expedited reporting, as described in Section 11.3.6, is required for SAEs, but not required for nonserious AEs or laboratory abnormalities.

#### **11.3.4.1 Assessment of Intensity**

The investigator will make an assessment of intensity for each AE and assign it to one of the following categories, and where appropriate, in accordance with the CTCAE Version 5.0:

- Grade 1 (Mild): An event that is easily tolerated by the participant, causing minimal discomfort, and not interfering with everyday activities;
- Grade 2 (Moderate): An event that causes sufficient discomfort and interferes with normal everyday activities;
- Grade 3 (Severe): An event that prevents normal everyday activities. An AE that is assessed as severe should not be confused with a SAE. Severe is a category utilized for rating the intensity of an event; and both AEs and SAEs can be assessed as severe;
- Grade 4 (Life-threatening): A life-threatening event is to be reported as an SAE;
- Grade 5 (Death): Death is to be reported as an SAE.

An event is defined as “serious” when it meets at least 1 of the predefined outcomes as described in the definition of an SAE, NOT when it is rated as severe.

#### 11.3.4.2 Assessment of Causality

The investigator is obligated to assess the relationship between study treatment and each occurrence of each AE. The assessment will be “related,” or “not related” as per [Table 11](#) and captured in the eCRF.

A “reasonable possibility” of a relationship conveys that there are facts, evidence, and/or arguments to suggest a causal relationship, rather than a relationship cannot be ruled out. The investigator will use clinical judgment to determine the relationship.

Alternative causes, such as underlying disease(s), concomitant therapy, and other risk factors, as well as the temporal relationship of the event to study treatment administration will be considered and investigated.

The investigator will also consult the IB and/or Product Information, for marketed products, in his/her assessment. For each AE, the investigator must document in the medical notes that he/she has reviewed the AE and has provided an assessment of causality.

**Table 11 Definition of Causality Terms for Adverse Events**

| Term        | Definition                                                                                                                                                                                                                                                                                            |
|-------------|-------------------------------------------------------------------------------------------------------------------------------------------------------------------------------------------------------------------------------------------------------------------------------------------------------|
| not related | Not suspected to be related to the study treatment. AE could not medically (pharmacologically/clinically) be attributed to the study treatment under study in this clinical trial protocol. A reasonable alternative explanation must be available.                                                   |
| related     | Suspected to be related to the study treatment. AE could medically (pharmacologically/clinically) be attributed to the study treatment under study in this clinical trial protocol. In the absence of a reasonable alternative explanation, a relationship to the study treatment cannot be excluded. |

Abbreviations: AE = adverse event

#### **11.3.4.3 Other Data to Be Recorded for Adverse Events**

In additions to intensity and causality the following should be recorded in the eCRF for each AE:

- Action taken with study treatment due to AE;
- Other action taken;
- AE outcome.

#### **11.3.5 Follow-up of Adverse Events or Serious Adverse Events**

All ongoing AEs should be followed up for 8 weeks after the last administration of study treatment. Any ongoing study treatment related AEs, which should be followed until resolution, or stabilization. Any new SAEs occurring up to 8 weeks after the last administration of study treatment should be reported to the sponsor or designee according to Section [11.3.6](#).

#### **11.3.6 Reporting of Serious Adverse Events**

All SAEs must be reported according to International Council for Harmonisation of Technical Requirements for Pharmaceuticals for Human Use (ICH) GCP or local regulations, applying the regulation with the stricter requirements.

- **Within 24 hours of becoming aware of a SAE:**

[figure not shown]

Initial notification via any other means than a completed SAE form does not replace the need for the investigator to provide a completed SAE report form within the designated reporting time frames.

There may be instances when copies of medical records for certain cases are requested by the sponsor. In this case, all participant identifiers, with the exception of the participant number, will be redacted on the copies of the medical records before submission to the sponsor or designee.

There may be situations in which an SAE has occurred and the investigator has minimal information to include in the initial report to the sponsor or designee. However, it is very important that the investigator always assess causality for every event before the initial transmission of the SAE data to the sponsor or designee.

#### **11.3.6.1 Safety Reporting to Health Authorities, Independent Ethics Committees/Institutional Review Boards, and Investigators**

[figure not shown]

A SUSAR is a subset of SAE. The sponsor or designee will report SUSARs to appropriate regulatory authorities, investigators, and IEC/IRBs according to local applicable laws and regulations, including European Directive 2001/20/EC, Regulation (EU) No 536/2014, and FDA Code of Federal Regulations 21 CFR Parts 312 and 320.

#### **11.3.6.2 24/7 Medical Emergency Coverage for Urgent Protocol-related Medical Questions**

[figure not shown]

On this internet page, a list of country-specific toll-free telephone numbers are provided. Note that not all countries globally have access to toll-free numbers as indicated on the “24/7 Medical Help-desk” index. Countries without toll-free numbers need to dial the chargeable number as indicated above. Furthermore, there may be restrictions when calling toll-free numbers from a mobile phone.

#### **11.3.7 Laboratory Assessments**

All chemistry and hematology parameters will be analyzed using a central laboratory. Urinalysis will be performed using the local laboratory. The parameters listed in [Table 12](#) will be collected.

**Table 12 Clinical Laboratory Tests**

| Laboratory Testing Profile                                                          | Tests Included                                                                                                                                                                                                                                                                                                                                                                                                                                                                                                                                                                                                                                                                                                                                                                                                                                                                                                                                                                          |
|-------------------------------------------------------------------------------------|-----------------------------------------------------------------------------------------------------------------------------------------------------------------------------------------------------------------------------------------------------------------------------------------------------------------------------------------------------------------------------------------------------------------------------------------------------------------------------------------------------------------------------------------------------------------------------------------------------------------------------------------------------------------------------------------------------------------------------------------------------------------------------------------------------------------------------------------------------------------------------------------------------------------------------------------------------------------------------------------|
| Laboratory tests required prior to first study treatment dose only                  | QuantiFERON TB-gold test (or equivalent IGRA), HIV testing, hepatitis B serology (HBV PCR if required) including hepatitis B surface antigen and antibody and hepatitis B core antibody, hepatitis C serology, HCV antibodies, confirmatory HCV PCR, SARS-CoV-2 PCR, RF, CCP antibodies, FSH, serum pregnancy                                                                                                                                                                                                                                                                                                                                                                                                                                                                                                                                                                                                                                                                           |
| Blood chemistry                                                                     | Sodium, potassium, chloride, bicarbonate, total protein, blood urea nitrogen, serum creatinine, albumin, alkaline phosphatase, AST, ALT, total bilirubin, direct bilirubin, indirect bilirubin, calcium, GGT, creatine kinase, hs-CRP                                                                                                                                                                                                                                                                                                                                                                                                                                                                                                                                                                                                                                                                                                                                                   |
| Hematology                                                                          | Hemoglobin, hematocrit, WBC with differentials (monocytes, eosinophils, basophils, neutrophils, lymphocytes) as an absolute value, RBC count, platelet count, ESR                                                                                                                                                                                                                                                                                                                                                                                                                                                                                                                                                                                                                                                                                                                                                                                                                       |
| Urinalysis                                                                          | 
Local urine testing
 
Routine urinalysis will be performed locally with urine dipstick test (semi-quantitative “dipstick” evaluation of specific gravity, pH, glucose, protein, bilirubin, ketones, leukocytes, blood).
 
If the dipstick urine test indicates any abnormal findings, the urine sample will be sent to the central laboratory for further assessments, as appropriate (reflex testing).
 
Central lab urine testing (reflex testing)
 
Urine chemistry (albumin:creatinine and protein:creatinine ratios) to be performed if dipstick indicates protein;
 
Microscopy and/or culture to be performed if clinically indicated or if urinalysis results positive (blood, protein or leukocyte esterase/WBC)
 
Note: Urine hCG pregnancy testing for WOCBP; may be repeated more frequently than indicated if required by local practice, if a menstrual cycle is missed, or if potential pregnancy is suspected
 |
| Fasting lipid panel and glucose to be performed at Day 1/Week 0 Visit and EOT Visit | Fasting: glucose, total cholesterol, low density lipoprotein, high density lipoprotein, triglycerides                                                                                                                                                                                                                                                                                                                                                                                                                                                                                                                                                                                                                                                                                                                                                                                                                                                                                   |

Abbreviations: ALT = alanine aminotransferase; AST = aspartate aminotransferase; CCP = cyclic citrullinated peptide; EOT = End-of-Treatment; ESR = erythrocyte sedimentation rate; FSH = follicle stimulating hormone; GGT = gamma-glutamyl transferase; HBV = hepatitis B virus; hCG = human chorionic gonadotropin; HCV = hepatitis C virus; HIV = human immunodeficiency virus; hs-CRP = high sensitivity C-reactive protein; IGRA = interferon-gamma release assay; PCR = polymerase chain reaction; RBC = red blood cell; RF = rheumatoid factor; TB = tuberculosis; WBC = white blood cell; WOCBP = women of childbearing potential

### **11.3.8 Electrocardiogram Assessments**

Computerized 12-lead ECG recordings will be obtained at scheduled study visits after the participant has rested for at least 5 minutes in the supine position. ECG data will be submitted to a central laboratory for measurement.

### **11.3.9 Physical Examination**

A standard complete physical examination will be performed at the weeks specified in the SOA (Section 3, Table 1). The following parameters and body systems will be examined and any abnormalities described: height, weight, general appearance, skin (presence of rash), HEENT (head, ears, eyes, nose, throat), lungs (auscultation), heart (auscultation for presence of murmurs, gallops, rubs), lower extremity exam, abdomen (palpation and auscultation), neurologic (mental status, station, gait, reflexes, motor and sensory function, coordination) and lymph nodes. Any clinically significant changes from the Screening Visit will be recorded as AEs.

### **11.3.10 Vital Signs**

Body temperature, respiration rate, heart rate (measured after at least 5 minutes of rest in the supine position), and systolic and diastolic cuff BP (measured after at least 5 minutes of rest in the supine position) will be recorded according to the SOA (Section 3, Table 1). Automatic or manual devices may be used, but the same device will be used for any given participant throughout the study. The same arm will be used for all BP measurements. All devices must hold valid calibration documentation at the time of use.

#### **11.3.12 Data and Safety Monitoring Board**

An independent DSMB will be formed to review the benefit-risk profile of sonelokimab during the study and to independently safeguard the interests of study participants.

The DSMB will review selected safety and efficacy data across the study at predefined intervals. The DSMB may also be called upon ad hoc, for example for the review of potential study stopping events (see Section 9.4.2).

The DSMB will consist of at least 3 voting members and include expertise in rheumatology, dermatology, and infectious diseases. DSMB members may not participate in this trial as investigators or in any other capacity.

An experienced unblinded biostatistician will be appointed to support the DSMB process. The DSMB unblinded biostatistician will be independent from all staff involved in the evaluation of the study data reviewed by the DSMB. Unblinded data will be reviewed only in closed sessions of the DSMB that are not attended by any personnel involved in the conduct of the study or evaluation of the data.

The DSMB may make recommendations to the sponsor regarding continuation, modification, or termination of the study. All recommendations of the DSMB will be made in writing, and minutes of all DSMB discussions will be kept. Minutes of closed sessions will be kept confidential until the study end.

Further details on the DSMB's members, roles, and procedures to ensure trial integrity will be described in the DSMB charter.

#### **11.4 Overdose**

A drug overdose is defined as the accidental or intentional use of a drug or medicine in an amount that is higher than is normally used. Every overdose must be reported to ICON PVSS within 24 hours of awareness, using the reporting method similar to reporting SAEs as detailed in Section 11.3.6, irrespective of whether the overdose was associated with an AE/SAE.

Overdose in this study is specifically defined as any dose greater than the intended protocol dose (Section 10.1). In case of overdose, it is recommended that the participant be monitored for any signs or symptoms of adverse reactions or effects and appropriate symptomatic treatment be administered immediately.

### **11.5 Hypersensitivity Reactions and Anaphylaxis**

All protein therapeutics have the potential to be immunogenic. No anaphylactic reactions have been reported to date in patients exposed to sonelokimab.

As part of the safety monitoring strategy in this study, all sites will have immediate access to appropriate drugs and medical equipment to treat acute hypersensitivity and study personnel will be trained to recognize and treat hypersensitivity and anaphylaxis. Any potential cases of anaphylaxis will be defined and assessed using the criteria defined in the Second Symposium on the Definition and Management of Anaphylaxis in [Appendix 4](#) in Section 21.4 [[Sampson H.A. et al., 2006](#)].

### **11.6 Immunogenicity Assessments**

Antibodies to sonelokimab will be evaluated in serum samples collected from all participants according to the SOA (Section 3, [Table 1](#)). At dosing visits, the samples will be collected prior to dose administration. Details on the collection and shipping of immunogenicity samples are in the Laboratory Manual. These samples will be analyzed by the sponsor's designated laboratory.

The detection and characterization of antibodies to sonelokimab will be performed using a validated assay method by or under the supervision of the sponsor.

### **11.7 Pharmacokinetics**

Blood samples will be collected for the measurement of trough (pre-dose) serum sonelokimab levels at the visits specified in the SOA (Section 3, [Table 1](#)). At dosing visits, the samples will be collected prior to dose administration. Details on the collection and shipping of PK samples are in the Laboratory Manual. Samples for PK will be analyzed by the sponsor's designated laboratory.

## 12 STATISTICAL CONSIDERATIONS

### 12.1 Sample Size and Power

The sample size calculation is based on the primary efficacy endpoint (i.e., ACR50 response rate at Week 12 compared with baseline) with the primary comparisons of interest being: sonelokimab 120 mg Q2W (Arm 1) vs placebo (Arm 4), sonelokimab 60 mg Q2W (Arm 2) vs placebo (Arm 4), and sonelokimab 60 mg Q4W (Arm 3) vs placebo (Arm 4), and determined based on assumed ACR50 response rates as follows:

- 40% with each sonelokimab dose regimen;
- 10% with placebo.

The estimated response rates for sample size were based on past IL-17 inhibitors for the treatment of patients with PsA. The Cosentyx FUTURE 2 study showed that ACR50 was achieved in 35% of secukinumab 300 mg and 37% of secukinumab 150 mg, vs 6% in the placebo arm [McInnes I.B. et al., 2015].

A sample size of  $n = 40$  participants in each of the sonelokimab 120 mg Q2W, sonelokimab 60 mg Q2W, sonelokimab 60 mg Q4W, and placebo arms (therefore, 160 participants in total) results in a power of more than 80%, while assuming an overall 2-sided alpha of 0.025, a placebo ACR50 response rate of 10% and a difference in ACR50 response rate of 30% between placebo and each sonelokimab dose regimen. An additional 40 participants will be randomized in the adalimumab arm. The adalimumab treatment will be used as an active reference arm, however, no formal comparison of sonelokimab or placebo vs adalimumab is planned.

Eligible participants will be randomized in a 1:1:1:1:1 ratio to sonelokimab 120 mg Q2W (Arm 1), sonelokimab 60 mg Q2W (Arm 2), sonelokimab 60 mg Q4W (Arm 3), placebo (Arm 4), or adalimumab 40 mg Q2W (Arm 5). The total proportion of participants with previous use of biologic agents will be capped at 30%.

Due to the use of the full analysis set (FAS) with non-responder imputation, no accounting for dropout is required, therefore a total of approximately 200 participants will be randomized.

All calculations were performed in nQuery® Software version 8.5.1.0.

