#### **12.3.2.2 Type I Error Control for the Primary and Key Secondary Endpoints**

To adjust for multiple testing and to control the family-wise error rate, the Bonferroni-Holm method will be applied first to sonelokimab 120 mg Q2W (Arm 1) and sonelokimab 60 mg Q2W (Arm 2), followed by a step-down procedure to test for sonelokimab 60 mg Q4W (Arm 3). The

smaller of the p-values  $p_{\text{SLK120mgQ2W}}$  and  $p_{\text{SLK60mgQ2W}}$  will be compared to  $\alpha/2 = 0.025$ , and the greater p-value to  $\alpha = 0.05$ , where  $p_{\text{SLK120mgQ2W}}$  is the p-value resulting from the comparison between sonelokimab 120 mg Q2W (Arm 1) and placebo (Arm 4) and  $p_{\text{SLK60mgQ2W}}$  is the p-value resulting from the comparison between sonelokimab 60 mg Q2W (Arm 2) and placebo (Arm 4). If both  $p_{\text{SLK120mgQ2W}}$  and  $p_{\text{SLK60mgQ2W}}$  are significant then the testing procedure will continue with the key secondary endpoints. The Bonferroni-Holm procedure used for the primary endpoint will be applied to each key secondary endpoint sequentially. If the procedure passes all the key secondary endpoints for both doses then sonelokimab 60 mg Q4W (Arm 3) will be compared to  $\alpha = 0.05$  firstly for the primary endpoint and then sequentially through the key secondary endpoints.

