### 12.3.3 Secondary Endpoints

#### 12.3.3.1 Key Secondary Endpoints

For the key secondary endpoints the hypotheses to be tested are that the proportion of participants who achieve the endpoints described in Section 7.2.2 at Week 12 in the sonelokimab 120 mg Q2W, sonelokimab 60 mg Q2W, or sonelokimab 60 mg Q4W arms are different from that of the placebo arm.

As per the primary analysis, only the sonelokimab 120 mg Q2W, sonelokimab 60 mg Q2W, and sonelokimab 60 mg Q4W arms will be compared pairwise with placebo. The adalimumab arm will serve as a reference arm only. A comparison among dose arms sonelokimab 120 mg Q2W, sonelokimab 60 mg Q2W, or sonelokimab 60 mg Q4W is not planned.

The statistical methods that will be used to test these hypotheses will be the same as described for the primary endpoint. The analysis of the key secondary endpoint PASI90 will only include the subgroup of participants with PsO involving at least 3% BSA at baseline. This is expected to be between 50% and 67% of the FAS.

A non-responder imputation method will be used as described for primary analysis of the primary endpoint.

The analysis will be performed using the FAS.

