## 8 STATISTICAL METHODS

### 8.1 General Statistical Conventions

All statistical procedures will be completed using SAS version 9.4® or higher.

For continuous variables, descriptive statistics (number of observations, mean, standard deviation (SD), minimum (min), first quartile, median, third quartile and maximum (max) and 95% confidence intervals (CIs) as appropriate) will be presented. Summaries of hs-CRP and PK concentration will include the geometric mean (GM) and coefficient of variation (CV). The count of missing observations will be provided in all descriptive tables.

Categorical variables will be presented as counts and percentages with non-missing values in each category. The number of missing values will be presented as a separate category, if there is at least one missing value. Unless otherwise stated, all statistical testing will be two-sided and will be performed using a significance (alpha) level of 0.05. For all statistical analyses, p-values and 95% CIs will be provided. All sensitivity analyses will be regarded as exploratory and as such no formal adjustment for multiplicity will be made.

Number of decimal places will be presented as follow:

- continuous variables: for min and max, the decimals will be used as captured in the database; arithmetic mean, median and quartiles will be depicted with one more decimal than captured in the database; and SD will be depicted with two more decimals than captured in the database.
- categorical variables: percentages will be rounded to one decimal place and a percentage of 100% will be reported as 100%.
- the p-values will be rounded and displayed to 3 decimal places, values less than 0.001 will be displayed as 'p<0.001' and values higher than 0.999 will be displayed as 'p>0.999'.

This study has two parts Part A and Part B:

**Part A Analysis:** For Part A, summaries and analyses will be based on the data collected from the visits Week 0 to Week 12. Unless otherwise stated, the summary statistics and analyses will be presented for the following treatment groups:

- Sonelokimab 120 mg Q2W;
- Sonelokimab 60 mg Q2W;
- Sonelokimab 60 mg Q4W;
- Placebo;
- Adalimumab.
- Total sonelokimab (safety tables only)

**Part B:** For Part B no statistical testing will be performed. Summary statistics will be based on the data collected from the visits Week 12 to Week 24.

Unless otherwise stated, the summary statistics will be presented for the following treatment groups:

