#### **8.6.1.4 Multiplicity**

The following multiplicity adjustments will be used to control the overall type I error rate at 0.05 for the primary endpoint and key secondary endpoints. All sensitivity analyses will be regarded as exploratory and no formal adjustment for multiplicity will be made.

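### The sample-size text calls 0.025 the overall alpha when the plan uses 0.05, and its power of more than 80% does not hold for 60 mg Q4W, which has at most about 75–78% under the planned testing sequence

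*Combined protocol and SAP*

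**What the plan says.** Protocol 12.1 names three primary comparisons of interest: Arm 1 (120 mg Q2W), Arm 2 (60 mg Q2W) and Arm 3 (60 mg Q4W), each against placebo. It assumes ACR50 rates of "40% with each sonelokimab dose regimen" and "10% with placebo". It then says that 40 participants per arm "results in a power of more than 80%, while assuming an overall 2-sided alpha of 0.025". SAP 5.5 and the synopsis repeat that sentence.

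The testing plan is in Protocol 12.3.2.2 and SAP 8.6.1.4. The SAP says its adjustments are "used to control the overall type I error rate at 0.05 for the primary endpoint and key secondary endpoints", and SAP 8.1 says that, unless otherwise stated, "all statistical testing will be two-sided and will be performed using a significance (alpha) level of 0.05". Within the procedure, 0.025 is alpha/2: the smaller of the Arm 1 and Arm 2 p-values is compared with it, and the larger with 0.05. If both are significant on ACR50, the same two-arm Holm step is applied to ACR20 and then to PASI90. Arm 3 comes last. The condition in 12.3.2.2 begins "If the procedure passes all the key secondary endpoints for both doses then sonelokimab 60 mg Q4W (Arm 3" …, and Arm 3 is then tested at 0.05, ACR50 first. Protocol 12.3.3.1 limits PASI90 to participants with at least 3% BSA at baseline: "This is expected to be between 50% and 67% of the FAS".

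Neither document gives a power figure for Arm 3 under this sequence.

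**The concern.** The sample-size text and the multiplicity text give different values for the overall alpha, and both cannot be right.

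The single power figure also sits under a list of three primary comparisons. Nothing limits it to the two that are tested first. A reader would take it to cover 60 mg Q4W. Yet the plan contains no test of Arm 3 at 0.025: it is tested at 0.05, and only after six earlier rejections (three endpoints, two doses). Its chance of formal success is therefore a joint probability, which the calculation does not address.

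The primary objective covers all three regimens. If either Q2W arm misses any one of the three endpoints, the primary hypothesis for 60 mg Q4W is never formally tested. Someone relying on 12.1 could take that outcome for a negative result from a comparison with more than 80% power.

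**Working it through.** **Inputs, all from Protocol 12.1 and 12.3.2.2.** n = 40 per arm; ACR50 40% on each regimen and 10% on placebo; two-sided tests; Holm thresholds 0.025 and 0.05; Arm 3 at 0.05. The calculations are unadjusted, that is, without the sex and prior-biologic covariates.

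**1. The plan's own figure.** For a pooled two-proportion z-test, power = Φ[(d − z·se₀)/se₁].
- d = 0.30 and mean rate = 0.25
- se₀ = √(2 × 0.25 × 0.75/40) = 0.0968
- se₁ = √((0.09 + 0.24)/40) = 0.0908
- z = 2.241 for two-sided 0.025
- (0.30 − 2.241 × 0.0968)/0.0908 = 0.914, so power = 82.0%

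The stated figure reproduces for one comparison taken alone at 0.025. At 0.05 the same formula gives 88.8%.

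**2. Power under the planned sequence.** The three comparisons share one placebo arm. Given x placebo responders, the active arms are independent. Let A(x) and B(x) be the probabilities that one active arm gives p < 0.025 and p < 0.05. Averaging over x ~ Binomial(40, 0.10):
- one Q2W arm succeeds under Holm: A + AB − A²
- both Q2W arms succeed under Holm: 2AB − A²
- both succeed and Arm 3 has p < 0.05: (2AB − A²)·B

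The last line treats ACR20 and PASI90 as certain to pass. Those gates can only remove outcomes, so it is an upper bound for Arm 3. Exact enumeration gives:

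| Test | One comparison at 0.025 | Each Q2W arm, Holm | Both Q2W arms | Arm 3, upper bound |
|---|---|---|---|---|
| Wald logistic | 81.1% | 86.5% | 80.5% | 74.9% |
| Chi-square | 83.3% | 88.0% | 82.4% | 77.4% |
| Likelihood ratio | 85.3% | 88.8% | 83.1% | 77.9% |

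The Wald row uses Fisher's test where an arm has a 0% or 100% response rate, in line with SAP 8.6.1.1. Two other methods give lower bounds for Arm 3: 72.4% by a normal approximation with shared placebo (correlation 0.09/0.33 = 0.27) and 68.2% with Fisher's exact test throughout. Every method tried is below 80%.

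**3. The remaining gates.** The PASI90 subgroup is 40 × 0.50 = 20 to 40 × 0.67 ≈ 27 participants per arm, and both Q2W arms must succeed in it, after both have succeeded on ACR20. Neither document gives assumed ACR20 or PASI90 rates for this trial, so the further reduction has a known direction but no size.

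**4. Alpha, side by side.** Protocol 12.1, SAP 5.5 and the synopsis: overall 0.025. SAP 8.6.1.4: overall 0.05. Protocol 12.3.2.2: alpha/2 = 0.025 and alpha = 0.05. The sample-size text has put the name of the family-wise level on the first Holm step.

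**The case against.** The best defence is that the figure is a per-comparison calculation, correctly done at the stricter level. Its arithmetic is sound, it understates power for the two Q2W arms, and Arm 3 taken alone at 0.05 has about 89–90% power. The sequence is fully specified elsewhere, gatekeeping is legitimate, and a Phase 2 plan need not report joint power for the last hypothesis. Arm 3 would still have an estimate, confidence interval and nominal p-value. All of that stands. It does not rescue the word overall, and the text nowhere says that the figure is per comparison or stops short of Arm 3.

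Three stronger readings are not supported:
- **That 12.1 expressly claims more than 80% power for each comparison.** The reference there to each regimen qualifies the assumed 30-point difference. Coverage of Arm 3 is an implication of listing it as a primary comparison.
- **That dropout takes Arms 1 and 2 below 80%.** If an assumed 10% dropout lowered the rates to 36% and 9%, one comparison at 0.025 would have 74% (Wald) to 77% (chi-square) power. That ignores Holm, under which each Q2W arm keeps 80.0% (Wald), 82.6% (chi-square) or 83.7% (likelihood ratio). The endpoint already counts discontinuation and missing Week 12 data as non-response, so 40% and 10% are naturally read as composite rates.
- **That a definite power for Arm 3 after all gates can be quoted.** It would rest on ACR20 and PASI90 rates that the documents do not supply.

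The ceiling also depends on the planning rates. At 36% versus 6%, close to the secukinumab results cited in 12.1 (35% and 37% versus 6%), it would be 82–87% by the three tests tabulated, still before ACR20 and PASI90. The plan chose 40% and 10%, and its statement has to be judged on those.

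**Conclusion.** The point holds as a misstatement in the sample-size text; the arithmetic and the testing procedure are not at fault. The overall two-sided alpha is 0.05. Power above 80% is right for Arms 1 and 2: about 82% for one comparison at 0.025 (81–85% by the exact calculations tabulated) and about 86–89% for each arm under Holm. For 60 mg Q4W, formal success on ACR50 has probability of at most about 75–78% at the plan's own rates and sample size, and lower once ACR20 and PASI90 are counted.

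The alpha conflict needs no assumption. The ceiling rests on 40% versus 10%, 40 per arm, a shared placebo arm, no covariate adjustment, and ACR20 and PASI90 passing with certainty. Type I error control and the planned estimates are unaffected.

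**What to change.** In Protocol 12.1, SAP 5.5 and the synopsis:
- state the overall two-sided alpha as 0.05;
- state that power above 80% (about 82%) is per comparison at 0.025, the first Holm step, for Arms 1 and 2;
- state that power for Arm 3 on ACR50 under the planned sequence is at most about 75–78% before the ACR20 and PASI90 gates, and lower after them by an amount not quantified.

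Leave the testing procedure and sample size unchanged. The cost is a text edit in three places and a less favourable figure for Arm 3, with no additional participants.
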